### Data collection

Patient demographics and clinical data will be obtained from the Stanford Translational Research Integrated Database Environment (STRIDE). STRIDE is a clinical data warehouse that is maintained by the Stanford University School of Medicine and is updated in near real time directly from the EMR used at Stanford Health Care. All data generated from the study will be managed and stored using REDCap electronic data capture tools, hosted by Stanford University. REDCap (Research Electronic Data Capture) is a secure, web-based application designed to support data capture for research studies [12].

### Study endpoints

#### Primary

The following endpoints will be evaluated:Difference in compliance rates with preventative turning practices between the treatment and control groups, as continuously measured by the Leaf Patient Monitoring System during the patients’ ICU stayDifference in the proportion of HAPUs between the treatment and control groups

#### Secondary

Secondary measures are to:Evaluate and describe, any differences identified in hospital-acquired pressure ulcer rates and stages between medical and surgical patient groupsDevelop explanatory models of contributing clinical factors to HAPUs for the three groups: all ICU patients, medical patients only, and surgical patients only

### Sample size calculation

Using a two-sided *Z* test of the difference between proportions with 80 % power and a 5 % significance level, a sample size of 1812 patients, 906 in each group, will be sufficient to detect a clinically important difference of 50 % between the groups in the rate of HAPUs. This assumes that a 50 % difference represents a change from a prevalence rate of 5 % for pressure ulcers in the control group, to a rate of 2.5 % for pressure ulcers in the treatment group. Conservatively, with an estimated enrollment of 200 subjects per month, study enrollment is expected to be between 7 and 10 months’ duration.

### Statistical analysis

Data analysis will be conducted using IBM SPSS Predictive Analytics Software (v20, Armonk, NY, USA), after data cleaning and organization within Excel 2010 (Microsoft, Seattle, WA, USA). A consultant statistician, external to the study team and trained in quantitative methods will oversee data analyses.

#### Descriptive analysis

Demographic and clinical characteristics will be summarized for each treatment group and reported. Frequencies will be determined for count data, such as the proportion of patients with pressure ulcers, and descriptive summaries will be used for continuous data, such as percentage of compliance time. Measures of central tendency (mean, standard deviation, median, minimum, and maximum values) will also be reported.

#### Primary endpoint

An independent-samples Student’s *t* test will be used to evaluate for differences in preventative turning compliance between the two groups. To test for differences in pressure ulcer rates between the treatment groups, a 2 × 2 table with chi-square statistic will be used. To further evaluate for differences in pressure ulcer rates between treatment groups over time, a Kaplan-Meier survival analysis with log-rank test will be used. For all analyses, tests are deemed to be significant if significance is less than *p* <0.05. Device-related pressure ulcers from catheters or tubes are generally unrelated to turning and are not included in this analysis.

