### Randomization

All subjects will be randomly assigned, with the aid of a computer-generated schedule, to receive either standard care (control group) or optimal pressure ulcer preventative care (treatment group). To minimize the risk of predicting the treatment assignment, randomization is performed in permuted blocks of two, four, and six, with random variation of block sizes. To minimize bias at the patient level, randomization is further stratified by unit of admission and admitting service, either medicine or surgery (Fig. 1). Once randomized, each subject will receive a nominal study identification number based on the unit of admission and admitting service. The lowest available number will be provided to each subject in sequential order.

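### Randomization is stratified by unit and admitting service, but the named primary tests for compliance and HAPU proportion ignore the strata; if the strata are prognostic, these tests are conservative and lose a little precision

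*Protocol article*

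**What the plan says.** The Randomization section of the protocol article states that "randomization is performed in permuted blocks of two, four, and six, with random variation of block sizes", and that "randomization is further stratified by unit of admission and admitting service, either medicine or surgery". Two units by two services make four strata, with the arms kept nearly equal in each.

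The Primary endpoint paragraph under Statistical analysis names three tests:

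- **Compliance:** an independent-samples Student's t "test will be used to evaluate for differences in preventative turning compliance between the two groups".
- **HAPU proportion:** "To test for differences in pressure ulcer rates between the treatment groups", "a 2 × 2 table with chi-square statistic will be used".
- **HAPU over time:** "a Kaplan-Meier survival analysis with log-rank test will be used".

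The first two are unstratified by construction. For the third, nothing is said either way.

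Admitting service enters only the secondary work: a Kruskal-Wallis comparison of ulcer stages by service, and separate explanatory models for medical and surgical patients. Unit of admission enters no named analysis.

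**The concern.** Stratified permuted blocks balance the arms within each stratum. If the strata predict the outcome, this removes between-stratum variation from the difference between arms. A crude t test or chi-square still counts that variation as error, so its standard error is larger than the true sampling variation under this design. Actual type I error then falls below 5% and some power is lost.

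The protocol gives some reason to expect this for one factor and one endpoint. It makes medical versus surgical differences in HAPU rates and stages a secondary measure, and it plans separate models for the two services. At stake is the precision that stratifying was able to buy, in a trial sized at 80% power with no margin shown.

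**Working it through.** **1. The plan's own figure.** The Sample size calculation section uses a two-sided Z "test of the difference between proportions with 80 % power and a 5 % significance level", with 5% against 2.5%. With pooled variance under the null and no continuity correction:

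n = [1.960 × √(2 × 0.0375 × 0.9625) + 0.8416 × √(0.05 × 0.95 + 0.025 × 0.975)]² / 0.025²
= [0.5266 + 0.2256]² / 0.000625 = 905.4, rounded up to 906 per arm.

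This matches the stated 906 per arm (1812 in total), and power at 906 is 80.0%. The sample size is not at fault.

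**2. HAPU proportion.** The documents give no stratum rates or stratum sizes, so the following are assumptions: four equal strata, arms balanced within each, control rates averaging 5%, and risk halved on treatment. Each row rests on 200,000 simulated trials with 906 per arm. R² is the between-stratum variance of the control rate divided by 0.05 × 0.95. For 1/2/5/12%, for example, it is [(16 + 9 + 0 + 49)/4] × 10⁻⁴ / 0.0475 = 0.039.

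| Control rates by stratum | R² | Power, crude chi-square | Power, CMH | Type I error, crude | Type I error, CMH |
|---|---|---|---|---|---|
| 5/5/5/5% | 0 | 80.7% | 80.7% | 4.97% | 4.97% |
| 2/4/6/8% | 0.011 | 81.0% | 81.3% | 4.9% | 5.0% |
| 1/2/5/12% | 0.039 | 81.3% | 82.1% | 4.6% | 5.0% |
| 0/0/0/20% (extreme) | 0.158 | 82.6% | 85.7% | 3.3% | 4.9% |

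CMH is the Cochran-Mantel-Haenszel test. The crude standard error is too large by about 0.5% in the second row, 1.7% in the third and 7–9% in the last. With equal rates, stratifying costs nothing.

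**3. Compliance.** Let R² be the share of compliance variance explained by the four strata. No value is given, so a range is shown. With balanced strata:

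- ratio of the crude standard error to the true one: f = 1/√(1 − R²)
- actual type I error of the crude test: 2 × [1 − Φ(1.960 f)]
- crude power where the adjusted analysis has 80%: Φ(2.802 − 1.960 f)

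| R² (assumed) | f | Standard error too large by | Type I error | Crude power |
|---|---|---|---|---|
| 0 | 1.000 | 0% | 5.0% | 80.0% |
| 0.05 | 1.026 | 2.6% | 4.4% | 78.5% |
| 0.10 | 1.054 | 5.4% | 3.9% | 76.9% |
| 0.20 | 1.118 | 11.8% | 2.8% | 72.9% |

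**4. Time to HAPU.** No calculation was made. The article does not say whether the log-rank test is stratified.

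**The case against.** The case for leaving the tests alone has four parts.

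- **Validity is safe.** In every scenario the crude tests err towards caution. A reader might infer that ignoring the strata invalidates the primary tests or raises the false-positive rate. The calculations show the opposite. This part stands in full.
- **The endpoint that sizes the trial hardly changes.** The planned chi-square matches the Z test used for the sample size, and the crude test still reaches 80% power in every HAPU scenario above. This stands too.
- **Compliance is probably not short of precision.** The Background reports a rise from 64 to 98% in a previous study of the system. Assume a standard deviation of 30 points (not in the documents). The standard error is then 30 × √(2/906) = 1.4 points, so a 10-point difference is about 7 standard errors. The crude 95% half-width of 2.8 points would shrink only to about 2.6 at R² 0.10, or 2.5 at R² 0.20. This largely stands. The Discussion admits that nurses may carry turning practice between arms, which could shrink the effect, but the conclusion would change only if the difference were very small.
- **The documents do not show that the strata matter for compliance.** What they say about service concerns HAPU, and they state no expected difference between the two units. A reader might infer that unit habits drive compliance, or that all three primary tests are unstratified. The text supports neither, and a condensed article may leave the log-rank detail to the full plan.

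The mismatch itself remains. The t test and the single 2 × 2 table are fixed by name, so for these two the article has made a choice and has not merely left detail out.

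**Conclusion.** The point holds as a matter of efficiency and of consistency between design and analysis, conditional on the strata being prognostic. It is not a threat to validity.

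For HAPU the loss is about 0 to 1 power point over the less extreme rate patterns, and about 3 points if all events fall in one stratum. For compliance it ranges from nothing to a standard error 11.8% too large as R² runs from 0 to 0.20.

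The mismatch can be read directly from the text. The magnitudes cannot: they rest on assumed stratum rates, equal stratum sizes and assumed R² values. The change is still worth making because it costs almost nothing if the strata turn out not to matter and recovers precision if they do.

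**What to change.** Amend the Primary endpoint paragraph before the data are analysed:

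- **HAPU proportion:** a Cochran-Mantel-Haenszel test stratified by unit × service, with a common risk difference or risk ratio. About 68 events are expected (906 × 0.05 + 906 × 0.025), or 17 per stratum if they are spread evenly, so a method that pools across strata is suitable.
- **Compliance:** a linear model with arm plus the four strata, for both planned compliance measures.
- **Time to HAPU:** state that the log-rank test is stratified by the same factors.
- **Sensitivity:** keep the crude t test, chi-square and unstratified log-rank test as supporting analyses.

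The cost is analysis wording only. Both factors are recorded at randomization, no further data are needed, and the sample size of 1812 stands.

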### Recruitment/Intervention

Upon admission to a study unit and as part of standard care, the patient receives a complete “head-to-toe” assessment of their skin. This is performed by two registered nurses (RNs). Any pre-existing pressure ulcer that is detected during this assessment is documented in the electronic medical record (EMR). After initial standard admission procedures are performed, and within the first hour of arrival, nursing staff will place a patient sensor (Leaf Healthcare, Pleasanton, CA, USA) in a predefined location on the patient’s chest (Fig. 2). If an exclusion condition is present, this will be documented and the patient will not be enrolled in the study and will not receive a patient sensor.

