#### Secondary endpoint

To test for differences in HAPUs between patients based on admitting service (medical or surgical), a Kruskal-Wallis rank test will be used. Stages of pressure ulcers (based on NPUAP staging criteria) will represent the ranks to be measured. A difference will exist if the significance level of the test statistic is *p* <0.05.

In creating explanatory models, multivariate logistic regression will be used. First, univariate testing of each variable in relationship to the endpoint (hospital-acquired pressure ulcer) will be performed. Only variables having a maximum significance with the endpoint of *p <*0.20 will be included in the multivariate model. Age and sex will be reintroduced to the models if they fail to meet the inclusion criteria and all other variables will be entered into the model in a forward stepwise fashion. This will be rerun until only significant variables remain. Three logistic regression models will be constructed: all ICU patients, only medical patients, and only surgical patients.

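### The primary pressure-ulcer test is valid but unadjusted; a prespecified model using the skin finding already recorded on arrival would be a small, cheap improvement

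*Protocol article*

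**What the plan says.** All places are in the protocol article.

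- **Statistical analysis, Primary endpoint.** The between-arm ulcer comparison is fixed: a 2 × 2 "table with chi-square statistic will be used". In support, a "Kaplan-Meier survival analysis with log-rank test will be used". Neither is described with covariates or strata.
- **Recruitment/Intervention.** Two nurses examine the whole skin on admission. "Any pre-existing pressure ulcer that is detected during this assessment is documented in the electronic medical record". The section places this step before the sensor is applied. Study population does not exclude patients who arrive with an ulcer, so the finding varies between patients.
- **Data collection.** Demographic and clinical data come from the hospital's data warehouse. No baseline risk score is named.
- **Randomization.** Allocation is stratified by unit and admitting service.
- **Descriptive analysis.** Demographic and clinical characteristics will be summarised by arm.
- **Secondary endpoint.** Logistic models are built by univariate screening at p < 0.20 and forward stepwise entry. "Age and sex will be reintroduced to the models" if they fail the screen. Treatment arm is not named as a term to be kept.
- **Sample size calculation.** A two-sided Z "test of the difference between proportions with 80 % power and a 5 % significance level" gives 906 per group, assuming "a prevalence rate of 5 % for pressure ulcers in the control group" and 2.5% under treatment.

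**The concern.** Skin status on arrival is a plausible predictor of a new ulcer. The article itself points that way: the Background notes that existing ulcers can restrict the positions available to a patient, and the secondary aims include modelling the clinical factors behind HAPUs. Yet the main test uses no patient-level baseline information.

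Two things are at stake, both modest. The first is precision. The trial is sized at 80% power with no stated allowance for loss, and the Discussion accepts that nurses may carry the optimised turning over to control patients, which would shrink the effect. The second is robustness. Suppose more patients with damaged skin fall by chance into one arm. The stepwise models are not designed to estimate the arm effect, so any adjusted arm effect would then be chosen after the data were seen, in an open-label trial. A model named in advance removes that difficulty whatever the size of the power gain.

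**Working it through.** **1. The plan's own figure.** Inputs from Sample size calculation: 5% against 2.5%, two-sided 5%, 80% power. The mean rate is (0.05 + 0.025)/2 = 0.0375. With the pooled-variance Z formula:

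n per arm = [1.96 × √(2 × 0.0375 × 0.9625) + 0.8416 × √(0.05 × 0.95 + 0.025 × 0.975)]² / 0.025² = [0.5266 + 0.2256]² / 0.000625 = 905.4, so 906.

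The stated figure is reproduced, with power 80.0%. Expected ulcers: 906 × (0.05 + 0.025) = 67.95, about 68 (45 against 23).

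**2. Power gained from the skin finding alone.** The article gives no prevalence q of pre-existing ulcers and no strength of association, so both are assumed. The share of outcome variance explained at the mean rate is

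R² = q(1 − q) × (risk gap)² / (0.0375 × 0.9625),

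and power after adjustment is approximately

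Φ{[0.025/√(1 − R²) − 1.96 × 0.00893] / 0.00891},

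where 0.00893 = √(2 × 0.0375 × 0.9625/906) and 0.00891 = √[(0.05 × 0.95 + 0.025 × 0.975)/906]. With R² = 0 this returns 80.0%.

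*Prevalence 5–20%, odds ratio 2–5, by formula.* R² runs from 0.0015 (5%, odds ratio 2) to 0.0273 (20%, odds ratio 5). Power runs from 80.1% to 81.1%.

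*Prevalence 10–30%, risk ratio 3–6.* Simulation (4,000 trials each) of crude chi-square against Mantel-Haenszel stratified by pre-existing ulcer, with the formula as a check:

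| Prevalence, risk ratio | Crude | Adjusted | Simulated gain | R² | Power by formula |
|---|---|---|---|---|---|
| 10%, 3 | 80.6% | 81.2% | 0.6 | 0.010 | 80.4% |
| 15%, 4 | 80.0% | 81.0% | 1.0 | 0.021 | 80.9% |
| 20%, 5 | 81.4% | 82.6% | 1.2 | 0.031 | 81.2% |
| 30%, 6 | 81.2% | 82.9% | 1.7 | 0.033 | 81.3% |

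Worked line for 15% and risk ratio 4: risk without an ulcer on arrival is 0.0375/(0.85 + 0.15 × 4) = 0.0259; gap = 3 × 0.0259 = 0.0776; R² = 0.1275 × 0.0776²/0.0361 = 0.021.

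Simulation error is about √(0.8 × 0.2/4000) = 0.6 points on each power figure, so the gains should not be read to the decimal. Taken together, the gain is about 0.1 to 1.7 points.

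**3. Validity.** In a separate simulation (10% prevalence, odds ratio 3, skin finding only), type I error was 5.2% for the chi-square and 5.4% for the adjusted logistic test. Power was 81.1% against 81.6%. Both tests hold their level.

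**4. Chance imbalance.** Assume 15% prevalence and risk ratio 4 in both arms.

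- Control: 0.05/1.45 = 0.0345 without and 0.1379 with an ulcer on arrival; gap 0.1034.
- Treatment: half of each; gap 0.0517.
- Standard deviation of the prevalence within one arm: √(0.15 × 0.85/906) = 0.0119.
- Standard deviation of the resulting shift in the crude difference: √(0.1034² + 0.0517²) × 0.0119 = 0.0014, or 0.14 points. That is 0.137/2.5 = 5.5% of the target difference.

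Applying the control-arm gap to both arms would overstate this. The standard error of the crude difference is 0.89 points, so imbalance in this covariate makes up about (0.137/0.89)² = 2% of its variance.

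**5. Room for covariates.** Arm, unit, service, pre-existing ulcer and age are five coefficients: 68/5 = about 14 expected ulcers per coefficient. A long covariate list would not be supported.

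**The case against.** The strongest reply is that nothing here is wrong. An uncorrected chi-square on 906 per arm is valid under randomization, and it is the counterpart of the Z test used for sizing. Stratification by unit and service already balances part of the case mix. The variability from chance imbalance is already allowed for in the error rate of the crude test. A crude primary analysis with an adjusted supporting one is as legitimate as the reverse, and the gain rests on assumptions that the article does not anchor. All of this stands, and it is why the point is put as an improvement.

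It could also be said that a journal article may leave an adjusted supporting analysis to a fuller document. That is fair for a supporting analysis. But the primary test is named outright, and the only regression described is stepwise without arm as a fixed term.

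A reader might infer more than the documents support:

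- *That the crude test is biased or invalid.* It is neither.
- *That several points of power are being lost.* That would need a moderate to strong baseline risk score, and the article names none. Such gains cannot be credited to pre-existing ulcer and age.
- *That an imbalance would go unseen.* Descriptive analysis promises clinical characteristics by arm, which is where it should appear.
- *That adjustment is free.* It needs no new data, but it brings a model assumption into the result.

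**Conclusion.** The point holds as a cheap improvement. The primary ulcer comparison is valid but leaves unused a baseline finding recorded on arrival, and no adjusted arm comparison is described. Adjusting for that finding alone adds about 0.1 to 1.7 points to 80% power, if prevalence lies between 5% and 30% and the odds or risk ratio between 2 and 6. The top of that range needs 30% prevalence and a risk ratio of 6. A one-standard-deviation imbalance moves the crude difference by about 0.14 points under 15% prevalence and a risk ratio of 4. The firmer benefit is that the adjusted arm effect would be named in advance. These gains would not offset a material dilution of the effect by carry-over of turning practice.

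**What to change.** In Statistical analysis, Primary endpoint, before outcomes are compared, name one prespecified logistic model for HAPU with these terms only: arm, unit of admission, admitting service, pre-existing pressure ulcer on arrival (yes/no) and age. Report the arm effect as a standardised (marginal) risk difference and risk ratio with 95% CI, and show the crude chi-square beside it. The marginal scale keeps the result comparable with the 5% against 2.5% target. State which of the two results is primary. If the sponsor keeps the chi-square as primary, the same model should be prespecified as the supporting analysis. State also how an undocumented skin finding is coded and how the standardised estimates and their intervals will be computed.

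Cost: wording and some programming. No patients, visits or data items are added. The downside is a model assumption with only about 68 expected ulcers, so the list should not grow; the crude table beside it lets the reader see whether the model matters. The article reports the trial as open to enrolment, so the change should be dated and made soon.

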**Fig. 3 Fig3:**
[figure not shown]
User-Dashboard – Leaf Patient Monitoring Interface. *Used with permission from Leaf Healthcare, Inc.

If the subject is enrolled in the control group, the unit secretary will turn the User-Dashboard “off” by selecting the “control patient” check-box in the Leaf Patient Monitoring System. This will turn the sensor information off and therefore not display any information to the User-Dashboard. Patients in the control group will continue to receive standard care practices, that is, pressure ulcer-prevention activities initiated by nurses using their usual care routines. Nursing care will not be “optimized” by the Leaf Patient Monitoring System, with the system withholding any data related to turning frequency, position schedule, and decompression time. The patient sensor will continue to collect these data for the purposes of research analysis only.

Each patient’s participation within the study begins within the first hour of arrival to a study unit and ends upon discharge or transfer from the study unit. Upon leaving the unit, the patient sensor will be removed and the patient will be discharged automatically from the Leaf Patient Monitoring System.

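### Kaplan-Meier curves with follow-up ending at ICU exit would overstate the proportion of patients who acquire an ulcer; cumulative incidence curves should be shown instead

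*Protocol article*

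**What the plan says.** The Study endpoints section makes the difference between arms in the proportion of hospital-acquired pressure ulcers (HAPUs) one of two primary endpoints. Under Statistical analysis, Primary endpoint, the main test of that proportion is simple: "a 2 × 2 table with chi-square statistic will be used". A second analysis follows. Its aim is worded "To further evaluate for differences in pressure ulcer rates between treatment groups over time", and its method is "a Kaplan-Meier survival analysis with log-rank test will be used".

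The Recruitment/Intervention section fixes the observation window. Participation starts within an hour of arrival and "ends upon discharge or transfer from the study unit".

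The Sample size calculation assumes "a prevalence rate of 5 % for pressure ulcers in the control group", changing "to a rate of 2.5 % for pressure ulcers in the treatment group". So 95% of control patients and 97.5% of treated patients are expected to leave without an ulcer. The article names no method that treats unit exit or death as a competing event. It does not say how either is to be handled in the time-to-event analysis.

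**The concern.** With follow-up closed at unit exit, ordinary Kaplan-Meier has only one place for a patient who leaves ulcer-free: censored at exit. That is nearly the whole trial. The estimator then spreads the ulcer risk of those still in the unit over those who have gone, as if they were still there and still exposed. A patient who has died or left can no longer acquire an ulcer in the unit, so the resulting 1-KM is not a probability that applies to the admitted patients.

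A time curve for a proportion endpoint should climb to that proportion by the end of stay. The cumulative incidence function does this. 1-KM keeps climbing beyond it. A published curve well above the 5% in the trial's own 2 × 2 table would contradict the table, and any absolute benefit read off it would be too large.

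**Working it through.** **The plan's own figure.** The stated basis is a "two-sided *Z* test of the difference between proportions with 80 % power and a 5 % significance level". For 5% against 2.5%, with pooled proportion 0.0375:

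n = [1.960·√(2·0.0375·0.9625) + 0.842·√(0.05·0.95 + 0.025·0.975)]² / 0.025² = 905.4, rounded up to 906 per arm.

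This reproduces "a sample size of 1812 patients, 906 in each group". It uses crude proportions only, so the choice of curve does not affect it.

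**Inputs for the curves.**
- Ulcer proportion by end of stay, p: 5% control, 2.5% treatment (Sample size calculation).
- Mean ICU stay, L: not in the documents, so an assumption, taken from 3 to 8.8 days. The upper end is a rough ceiling from 58 beds (Discussion) and 200 enrolments a month (Sample size calculation): 58 × 30.4 / 200 = 8.8 days at full occupancy. Enrolment over 7 to 10 months would put this ceiling at 6.8 to 9.7 days.
- Constant hazards, and exit independent of ulcer risk: assumptions.

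**Formulas.** Exit hazard μ = 1/L. The ulcer hazard that yields p by end of stay is h = pμ/(1−p). Then:
- 1-KM(t) = 1 − exp(−ht)
- true cumulative incidence CIF(t) = p·[1 − exp(−(h+μ)t)]
- still at risk, of 906: 906·exp(−(h+μ)t)

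**Example: control arm, L = 4, day 14.** h = 0.05 × 0.25 / 0.95 = 0.01316.
- 1-KM = 1 − exp(−0.1842) = 16.8%.
- CIF = 0.05 × [1 − exp(−3.684)] = 4.9%.
- At risk = 906 × exp(−3.684) ≈ 23.

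**Control arm, 1-KM against true cumulative incidence:**

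| Assumed mean stay | Day 3 | Day 7 | Day 14 | Day-14 ratio | At risk, day 14 |
|---|---|---|---|---|---|
| 3 days | 5.1% vs 3.3% | 11.6% vs 4.6% | 21.8% vs 5.0% | 4.4 | 7 |
| 4 days | 3.9% vs 2.7% | 8.8% vs 4.2% | 16.8% vs 4.9% | 3.5 | 23 |
| 5 days | 3.1% vs 2.3% | 7.1% vs 3.9% | 13.7% vs 4.7% | 2.9 | 48 |
| 8.8 days | 1.8% vs 1.5% | 4.1% vs 2.8% | 8.0% vs 4.1% | 2.0 | 170 |

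**Difference between arms, L = 4, day 14.** For treatment, h = 0.025 × 0.25 / 0.975 = 0.00641, so 1-KM = 8.6% and CIF = 2.4%. The gap is 16.8 − 8.6 = 8.2 points by 1-KM and 4.9 − 2.4, about 2.4 points unrounded, by cumulative incidence. The ratio of the arms is hardly changed: 16.8/8.6 = 1.96, against 2 in the plan.

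**Other shapes.** Weibull ulcer hazards (shape 0.5, 1 and 1.5) were combined with exponential or lognormal stay. The day-14 ratio ran from about 1.5 (early ulcers, 8.8-day stay) to about 7.2 (late ulcers, 3-day stay). No case removed the overstatement.

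**Log-rank test.** In 4,000 simulated trials per setting, with equal ulcer hazards and independent exit, it rejected in 5.7% with stays of 4 and 4 days, 5.1% with 4 and 3, and 5.7% with 5 and 3. Expected events under the plan are 906 × 0.075 ≈ 68. Power at a hazard ratio of 0.5 is about 0.82 by Schoenfeld's formula and 0.77 by simulation.

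**The case against.** **The analysis is supplementary.** This stands. The chi-square test carries the comparison of proportions, and no section says that absolute risks will be read from the curves. The point therefore concerns how results over time are displayed, not the trial's main test.

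**The log-rank test suits the stated aim.** This also stands. A reader might infer that the log-rank test is invalid, or that possible disagreement with the chi-square test is a defect. Neither follows. It compares the ulcer hazard among patients still in the unit, which is a fair reading of rates over time. It held close to its nominal level in the simulations even when stay differed by arm. Crude proportions do move with time at risk, so the two tests answer different questions.

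**The arithmetic does not show bias from informative exit.** Correct. It assumes independent exit, under which Kaplan-Meier estimates its own net-risk quantity properly. The gap is one of estimand: that quantity is not the trial's endpoint. Sicker patients staying longer may add bias, but the documents give nothing to size it.

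**The late part of the curve is nearly empty.** Correct. With a 4-day mean stay the formula gives 30.8% at day 28, but fewer than one of 906 control patients would still be at risk. That figure should carry no weight.

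**The censoring rule is inferred, and an article condenses.** Partly right. The rule follows from the named method and the stated end of participation, but a fuller document could define it otherwise. The method itself is stated, however, and any ordinary Kaplan-Meier curve that censors at unit exit has this property.

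**Ward transfer could be called loss of observation.** For an ulcer acquired anywhere in hospital, that is so. For an ulcer acquired during the monitored ICU stay, which is all the trial observes, exit is a competing event.

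**Conclusion.** The concern holds for the curves only. As planned, and with ulcer-free patients censored at exit in the ordinary way, 1-KM does not estimate the proportion of patients who acquire an ulcer and overstates it. At day 14 the control curve would read about 8% to 22% against a true 4% to 5%. The excess is modest in the first days, about 1.2 to 1.6 times at day 3. These ranges rest on constant hazards, the protocol's 5%, and assumed mean stays of 8.8 down to 3 days. The direction did not change under the other shapes tried.

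The documents do not support the stronger conclusions that the primary comparison is compromised, that the sample size is wrong, or that the log-rank test must be replaced.

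**What to change.** In the Primary endpoint paragraph of the Statistical analysis section:

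- Replace the Kaplan-Meier curves with Aalen-Johansen cumulative incidence of first HAPU by arm, with unit exit (discharge or transfer) and death as competing events. Show numbers at risk, so that the thin tail is visible.
- Keep the log-rank test, described as a comparison of ulcer hazard while in the unit.
- State how exit and death are handled in each analysis.
- Gray's test is optional. It compares cumulative incidence, so it also picks up any effect of the intervention on length of stay. With follow-up complete to exit, the curve ends at the crude proportion that the chi-square test already compares.

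The cost is a little extra analysis, possibly in software outside base SPSS, and the extraction of exit status and exit time for every patient. The admission-discharge-transfer feed described under Technology should supply discharge and transfer. The article does not say where death is recorded, so that source needs confirming. Enrolment, care and sample size do not change.
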